## Results

Between August 2014, and April 2017, 63 hospitals that met the selection criteria were invited, 36 (57%) of which were activated (ie, were trained, had access to database, were eligible to include patients), of which 29 (81%) enrolled patients.

A total of 1047 patients were collected during the trial period between January 1, 2015, and December 31, 2017. Follow-up data collection ended on December 31, 2019. Final results are expected to be published in 2020 or 2021.

## Discussion

### Summary

CIRT is the first European-wide prospective observational study of patients with liver tumors treated with radioembolization as the standard of care and will provide an important addition to the body of knowledge on radioembolization treatment.

Data from several large RCTs on mCRC and HCC were published while CIRT was already ongoing and more can be expected in the future [12,30,31]. However, these studies provide insufficient data with respect to “real life” clinical practice since there may be patient cohorts that benefit more from radioembolization than the patient cohorts included in these trials [32-34]. CIRT was designed to also explore patient cohorts for which less data is available. The writing group hopes that the outcomes of CIRT would provide valuable insights in these less explored patient populations to gain further insight into real world clinical practice of radioembolization. The extent to which this data relates to the overall body of data available on radioembolization will be discussed in the results publication.

### Limitations

The single-arm observational study nature of the study design implies that several limitations need to be considered. The absence of a contemporaneous comparator group may limit our interpretation of the clinical data reported. Despite this, important positive features of the study are the long-term data collection for patients included and the valuable information collected on health-related QOL. The size of the study should enhance patient selection by providing new information on the patient subgroups that benefit most from this treatment in day-to-day clinical practice.

Furthermore, selection bias could occur at several stages of the study. An element of site selection was introduced when the Steering Committee created a list of sites that met the selection criteria of minimal expertise with radioembolization treatment. The potential of patient selection bias is addressed by a contractual agreed upon prospective design, whereby sites agreed to present the possibility to participate in the CIRT to all eligible patients consecutively.

Another source for bias relates to drop-out during follow-up. The sites included in the study have been advised to continue patient follow-up at least 24 months after the first treatment. However, patients may be lost to follow-up or withdraw their consent at any time. Loss to follow-up may relate to the course of disease or site procedures; for example, when a patient is treated at a participating site but followed-up by their referring physician, sometimes in another country. It will therefore not always be possible for study sites to collect additional follow-up data and the patient will be reported as lost to follow-up. Baseline characteristics will be compared between those lost to follow-up and those who have follow-up data to assess differences with the potential to bias results. Notable differences on a background characteristic will prompt additional analyses where the sensitivity of the results to that background characteristic will be further assessed.

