### Data Collection

Patients enter the study by accepting participation and signing the informed consent form. Baseline data is collected upon allocation. Data on how the treatment was performed and its day-of-treatment outcomes are collected on the day of treatment. The patient is then followed for a maximum of 24 months or until study exit (see Figure 1). Guidelines for radioembolization advise that posttreatment assessments should be performed every 3 months [22]. However, the final decisions on treatment and follow-up schedules are determined by the site-specific medical teams.

Baseline assessments included patient demographics, medical history related to the underlying disease and cancer treatment, as well as cancer type and stage for patients with HCC (Table 1). The technical aspects that may determine how radioembolization is performed or impacts procedure-related outcomes were documented at the time of treatment. Time to event end points and safety end points were collected at every follow-up. In addition to demographic and clinical data, patient-reported outcomes are measured using the European Organisation for the Research and Treatment of Cancer (EORTC) quality of life questionnaire C30 (QLQ-C30) [23,24]. The questionnaire was provided before the treatment, shortly after the treatment, and at every follow-up. When this was not feasible on site, patients were approached via letters or phone calls organized by the study center responsible for the patient. For patients with HCC, in addition to the QLQ-C30, the HCC module was provided to assess factors related to chronic liver disease, as well as issues related to the primary tumor and its treatment [25]. The QLQ-C30 and HCC module were made available to each patient in their local language, using questionnaires translated and validated by EORTC [26-28].

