### Statistical Analysis

All patients who were found eligible, enrolled in the registry, underwent radioembolization treatment, and have the minimum amount of data required will be included in analysis. Patients for which the amount of data collected is too scarce to warrant meaningful analysis will be excluded. The number of excluded patients and reason for exclusion will be reported.

Data regarding the primary end point, safety, and technical considerations will be presented by summaries (eg, counts, means, standard deviations) and descriptive statistics. The number of missing observations will be given in all summary tables. Time to event end points will be described graphically through the Kaplan-Meier analysis (including 95% CIs for median survival). The Cox regression will be used to assess the impact of the covariates for time to event end points (Table 2).

Hazard ratios and their 95% CIs will be presented together with *P* values. Sensitivity analyses of time to event data will be performed where censored patients with less than 6 weeks of follow-up will be included as worst case (ie, death or progression).

**Table 2 table2:** Covariates for time to event end points.

Covariate	Variables
Age (years)	≤69 and ≥70
Sex	Male, female
Number of lines of previous chemotherapy	0, 1, 2-5, ≥6
Primary tumor in situ	Yes, no
Eastern Cooperative Oncology Group performance status	0, 1, and ≥2
Presence of extrahepatic metastases	Yes, no
Prior liver procedures	Yes, no
Number of liver tumors	1, 2-5, and ≥6
Percentage tumor to liver volume	Continuous

QOL is measured with the EORTC QLQ-C30, a questionnaire developed to assess the QOL in patients with cancer. The QLQ-C30 includes five functional scales, three symptom scales, a global health status scale, and six single items. The functional and symptom status of the QLQ-C30 will be assessed according to the scoring manual developed and validated by EORTC [29]. Patients who die during follow-up will be included in the QOL analyses until their date of death. The focus of these analyses will be on patients who are alive at the time point of analysis.

To document the safety and effectiveness of radioembolization and subsequent surgical or interventional procedures, the data will be broken down into subgroups as defined for the covariate analyses above.

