Missing data can be expected in the event of a study site failing to enter certain data into the e-CRF, or a patient’s withdrawal of consent or being lost to follow-up. Given the descriptive and exploratory nature of CIRT, all available data will be used, and no imputations of missing data will be made. The amount of missing data will be summarized and the subset of patients with missing data will be compared with patients included in the analysis.

In the effectiveness analyses, patients withdrawing consent or being lost to follow-up will be censored at the last time they were observed as being alive (overall survival) or at the time of their last magnetic resonance imaging scan from which disease progression could have been determined (progression-free survival [PFS]). Patients who die during the course of their follow-up in the registry will be regarded as having disease progression in the analyses of PFS and liver-specific PFS.

Missing data for QOL will be handled in line with the suggestions in the EORTC scoring manual for QLQ-C30; the amount of and reasons for completely missing forms will be analyzed and multiple imputations will be used for a part of the completely missing forms (ie, forms considered to be missing at random or due to administrative failure) [29].

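### The drop-out check compares patients lost with patients followed and takes no account of death, so it can mask or falsely suggest a loss rate that differs by prognosis

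*Protocol article*

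**What the plan says.** The Limitations section of the protocol article names drop-out as a source of bias and concedes that "Loss to follow-up may relate to the course of disease or site procedures". Its remedy has two steps. The first is a diagnostic: "Baseline characteristics will be compared between those lost to follow-up and those who have follow-up data to assess differences with the potential to bias results". The second is a rule that depends on it: "Notable differences on a background characteristic will prompt additional analyses where the sensitivity of the results to that background characteristic will be further assessed". The text does not define the two groups, say where deaths go, mention time at risk, or set a threshold for a notable difference.

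Three statements under Statistical Analysis bear on this:

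- Censoring: "patients withdrawing consent or being lost to follow-up will be censored at the last time they were observed as being alive (overall survival"). For progression-free survival (PFS), the censoring date is the last informative scan.
- A sensitivity analysis that does not depend on the diagnostic: "Sensitivity analyses of time to event data will be performed where censored patients with less than 6 weeks of follow-up will be included as worst". The outcome assigned to these patients is death or progression.
- A second comparison: "the subset of patients with missing data will be compared with patients included in the analysis". It has no stated consequence and no time scale.

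On follow-up, Data Collection says "The patient is then followed for a maximum of 24 months or until study exit". On the main method, Statistical Analysis says "Time to event end points will be described graphically through the Kaplan-Meier analysis", with Cox regression on the Table 2 covariates.

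**The concern.** Censoring at loss is harmless when, among patients still alive and under observation, the rate of loss is unrelated to prognosis. That rate is what a diagnostic should estimate.

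The proportion ever lost is a different quantity. A patient who dies early has little time in which to be lost and then sits in the comparison group. Characteristics that predict death therefore appear to protect against loss. If sicker patients leave faster while alive, the two effects can cancel, the table looks balanced, and the additional analyses by background characteristic are not prompted. If loss has nothing to do with prognosis, the table shows a difference and suggests that healthier patients are leaving. At stake is how the registry judges the reliability of its overall survival (OS) and PFS curves.

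**Working it through.** The documents state no loss rate, survival figure or threshold for this point, so there is no figure of the plan to reproduce. Only the 24-month horizon and N = 1047 come from the article. All hazards below are assumptions.

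**Proportion ever lost.** With constant monthly hazards of loss *l* and death *d*:

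P(lost by 24 months) = l/(l+d) × (1 − exp(−24(l+d)))

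| Group | l | d | Calculation | Ever lost |
|---|---|---|---|---|
| Better prognosis | 0.02 | 0.04 | 0.3333 × (1 − 0.2369) | 25.4% |
| Poorer, equal loss rate | 0.02 | 0.12 | 0.1429 × (1 − 0.0347) | 13.8% |
| Poorer, doubled loss rate | 0.04 | 0.12 | 0.2500 × (1 − 0.0215) | 24.5% |
| Poorer, doubled loss rate, lower death rate | 0.04 | 0.08 | 0.3333 × (1 − 0.0561) | 31.5% |

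**What the baseline table would show.** Assume that 20% of patients have the poorer prognosis and d = 0.12.

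- Equal loss rates: 0.2 × 0.138 = 0.0276 of all patients are poorer-prognosis and lost, out of 0.0276 + 0.8 × 0.254 = 0.231 lost overall. The poorer-prognosis share is 11.9% of the lost and 22.4% of the not lost. This difference is false.
- Doubled loss rate: 0.2 × 0.245 = 0.0489 out of 0.252 lost. The shares are 19.4% and 20.2%, so a true twofold difference does not show.
- With d = 0.08 the doubled rate does show, but understated: 31.5% against 25.4% ever lost.

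**Other survival assumptions.** The masking ratio is the loss-rate ratio (poorer to better) at which the 24-month proportions are equal. With loss of 0.01 to 0.03 per month in the better group:

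| Median OS, better/poorer (months) | Masking ratio |
|---|---|
| 12/8 | 1.30–1.33 |
| 18/9 | 1.46–1.53 |
| 20/6 | 2.09–2.26 |

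Between 1 and the masking ratio, the check points the wrong way.

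**Ever-lost test against a time-to-loss Cox model.** Simulation with 400 runs, N = 1047, equal groups, median OS 20/6 months, and loss of 0.02 per month in the better group:

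| True loss ratio | Ever-lost test rejects | Cox model rejects (mean HR) |
|---|---|---|
| 1 | 99.8%, always in the direction of poorer-prognosis patients lost less (OR 0.45) | 6% (0.99) |
| 1.5 | 75%, all in the wrong direction (OR 0.68) | 85% (1.49) |
| 2 | 9% (OR 0.93) | 100% (2.01) |

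**Effect on the survival estimate.** Take the masked case from the first table (20/80 mix, death 0.12/0.04, loss 0.04/0.02). True 24-month OS is 0.2 × exp(−2.88) + 0.8 × exp(−0.96) = 0.0112 + 0.3063 = 31.8%. Pooled Kaplan-Meier converges to exp(−∫h(t)dt), where h averages the two death hazards with weights 0.2 exp(−0.16t) and 0.8 exp(−0.06t). This gives 32.6%, an overstatement of 0.9 points before rounding. The median is overstated by about 0.3 months. At the masking ratios for median OS 18/9 and 20/6, the overstatement is about 0.3 to 3.3 points and 0.1 to 0.7 months.

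**Reach of the 6-week analysis.** At the masking ratios, about 11% to 17% of losses occur before 6 weeks (1.38 months).

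**The case against.** Several points on the other side stand.

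- **The groups are ambiguous.** A patient lost at month 12 also has follow-up data, so the contrast could mean no follow-up versus some. That fits the article's example of patients followed by a referring physician elsewhere. Over a 3-month window the masking ratio falls to 1.04–1.13 and the problem nearly vanishes. However, the sentence sits under drop-out during follow-up, where loss can happen at any time, and on the narrow reading the check would say nothing about later losses.
- **The check does not control every sensitivity analysis.** A reader might infer that a balanced table leaves OS and PFS with no sensitivity analysis. The documents do not support this: the 6-week worst-case analysis has no trigger. Only the additional analyses by background characteristic are conditional. The 6-week analysis does, however, leave later losses untested.
- **Serious bias does not follow.** A reader might infer that the survival results would be badly wrong. In the scenarios examined the error is modest. With equal loss rates Kaplan-Meier is unbiased, and the false difference costs an unneeded analysis and a possible misreading. Loss that depends only on Table 2 covariates does not bias correctly specified adjusted hazard ratios, and curves stratified by such a covariate are unaffected.
- **A better baseline screen is still a baseline screen.** Loss driven by the course of disease after treatment is invisible to any comparison of baseline characteristics, including a time-to-loss model. This is a reason not to make the further analyses depend on such a screen.

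The argument that this is detail left to an unseen analysis plan is weaker. The article states a specific contrast and a specific consequence, although nothing in it rules out accounting for time at risk.

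**Conclusion.** The point holds in limited form. Read as ever lost versus not lost, the planned comparison confounds the rate of loss with the rate of death. It can miss a higher loss rate in poorer-prognosis patients, reverse it, or show a difference where there is none. The direction of this distortion follows for any positive difference in death hazard. Its size depends on the assumed constant hazards, none of which the documents give, and near-exact masking of a doubled loss rate needed a threefold difference in death hazard.

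The consequence is a misleading diagnostic and a poor trigger for one set of analyses. It is not a demonstrated distortion of the main results. This is a cheap improvement.

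**What to change.** 1. Define the two groups, stating where patients who die, withdraw consent or are lost after some follow-up belong.
2. Replace the two-group comparison with a time-to-loss analysis. The event is loss to follow-up or consent withdrawal; patients are censored at death, month 24 or data cut-off. Report loss rates, or a cause-specific Cox model, by the Table 2 covariates, tumour type and site.
3. Run the loss-to-follow-up sensitivity analyses of OS and PFS whatever that analysis shows, and let them cover losses after 6 weeks. The time-to-loss results then help to interpret them and do not decide whether they are run.

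The cost is a wording change, one extra model and a small amount of added analysis. The dates are already needed for the planned censoring.

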### Conclusion

To date, the CIRT is the largest observational study on the use of radioembolization with 90Y resin microspheres. The objective of the study was to observe the real-life clinical application of radioembolization and its impact in clinical practice. Currently, radioembolization has a position in the guidelines for the treatment of HCC, cholangiocarcinoma, and mCRC, and more data is warranted on the possibilities that this treatment has for these diseases. Furthermore, additional data is needed for the effects of other lines of therapy and treatment of liver metastatic disease from other primary sites. Observing a large study population may reveal treatment aspects that would justify a wider application of this innovative treatment.

## Abbreviations

CIRSE: Cardiovascular and Interventional Radiological Society of Europe
CIRT: Cardiovascular and Interventional Radiological Society of Europe Registry for SIR-Spheres Therapy.
e-CRF: electronic case report form
EORTC: European Organization for the Research and Treatment of Cancer
HCC: hepatocellular carcinoma
mCRC: metastatic colorectal cancer
PFS: progression-free survival
QLQ-C30: quality of life questionnaire C30
QOL: quality of life
RCT: randomized controlled trials
SIR: selective internal radiation
90Y: yttrium-90.
